### Statistical analysis

No interim analysis is planned.

Baseline characteristics of patients will be described according to group of intervention. Continuous variables will be summarized using descriptive statistics, i.e. number of subjects, mean, median, standard deviation (SD), interquartile range, minimum and maximum. Qualitative variables will be summarized by frequency and percentage. Since this is a non-inferiority study, analysis of the principal criterion will be performed on a per-protocol population. Secondary analysis will be performed based on the intention-to-treat (ITT) principle. VTE events will be defined by: DVT (assessed by proximal compression ultrasonography) or PE (a CTPA or angiography showing intraluminal defect, or a V/Q lung scan showing a high-probability pattern). The decision rule will be based on the upper bound of the 90 % 2-sided CI of the difference of percentage of VTE events between groups. If the upper bound of the CI is above the 1.5 % of difference, the non-inferiority hypothesis of the intervention group will be rejected. The Dunnett and Gent chi square test will also be performed. Secondary analysis will be performed on the ITT population. Considering cluster randomization, confirmatory analysis will be performed using a generalized estimating equation (GEE) assuming an exchangeable correlation matrix structure and considering clustering at the site level. Secondary criteria will be compared under superiority hypothesis and on the ITT population. Descriptive analysis will be performed. Superiority approach will be used to compare secondary evaluation criteria between groups. The ED length stay and the mean proportion of hospital admissions following the ED visit will be compared using a mixed model, considering “center” as random effect. Unnecessary irradiative imaging, adverse events and deaths at 3 months will be compared using GEE assuming an exchangeable correlation matrix structure and considering clustering at site level. All superiority tests will be performed at 5 %. Pre-specified secondary analysis will include comparison of gestalt, Wells’ score and RGS, and performances of the PERC35 score for patients aged under 35 years [38]. Missing data will not be replaced except for the principal criteria for the secondary ITT analysis. Missing value will be considered as an event whatever the group randomized.

According to recent large European cohorts, we estimate that the primary endpoint rate in our control group will be 1.5 % [35, 36, 39]. To be regarded as non-inferior, the maximal difference in proportions between 2 groups (Delta) should not exceed 1.5 % – an absolute primary event rate of 3 % in the intervention group. This failure rate corresponds to the upper bound of the observed rate after a negative CPTA and is a widely accepted criterion for the validation of diagnostic strategies for PE [40]. This rate is in line with previous landmark studies that comprise the basis of our current understanding.

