### Trial objectives and outcomes

The primary objective of this study is to assess the non-inferiority of a PERC-based diagnostic strategy for ED patients with a low probability of PE based on physician’s gestalt, compared to the standard strategy of D-dimer testing, on the prevalence of undiagnosed VTE events. The secondary objectives are the following:to assess the reduction of unnecessary irradiative imaging studies and adverse eventsto assess the reduction in ED length of stayto assess the reduction of onset of anticoagulation regimen and associated adverse eventsto assess the reduction of hospital admission following the ED visit, hospital readmission, and mortality at 3 months.

The primary outcome is the percentage of diagnostic strategy failure, defined as diagnosed VTE at 3-month follow-up, among patients for whom PE has been initially ruled-out. Exclusion of PE in the ED is made based upon a negative D-dimer result or a negative CTPA in both groups, or a negative PERC in the intervention group.

Follow-up will be made by telephone interview of the patient or his general practitioner, and review of any outpatient consultation or hospital visit at 3 months (13 weeks) by a CRT. The time frame of the 3-month follow-up period could be subject to minor adjustments, but should occur between day 84 and day 98. Follow-up visit or interview will seek the occurrence of VTE events (DVT documented with ultrasonography of the lower limbs or venous computed tomography (CT), or PE documented with positive CTPA or high probability ventilation/perfusion (V/Q) lung scan), death, return visit to the ED, and hospitalization. All medical records pertaining to the patient within this timeframe will be sought and analyzed by the local investigator, looking for reports of VTE events, or adverse events from CTPA or anticoagulation. In case of death, report of a VTE, or major cardiovascular event, the file will be analyzed by a committee of three independent experts. This method of adjudication has been described and validated in all major previous PE diagnostic studies [35, 36].

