The primary criterion of a VTE event will be based on an objective diagnosis of DVT on Doppler ultrasonography, an intraluminal defect on CTPA, or a V/Q lung scan with a reported high probability. To confirm the occurrence of the primary endpoint, all files with evidence of a thromboembolic event collected by the local investigator of each center will be independently reviewed by an adjudication committee of three experts, blinded one to the other, and blinded to the study group. The adjudication committee will also review cases of death with no evidence of VTE event and will adjudicate whether or not the death is likely related to a PE. A sudden death in the absence of other obvious cause will be adjudicated as related to a PE. This committee will include three members, independent from the trial, with expertise in the field of PE, and will meet the recommendations of Dechartres et al. [37].

The result of adjudication regarding the primary endpoint, and other secondary endpoints at follow-up will be entered on the eCRF by a CRT or the local investigator.

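### The primary VTE event is defined inconsistently between the outcome and analysis sections, and neither says whether an adjudicated PE-related death counts

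*Protocol article*

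**What the plan says.** All places are in the protocol article.

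- **Headline outcome** (Trial objectives and outcomes): diagnostic failure, "defined as diagnosed VTE at 3-month follow-up, among patients for whom PE has been initially ruled-out". Death is not mentioned.
- **What follow-up looks for** (same section): "DVT documented with ultrasonography of the lower limbs or venous computed tomography (CT), or PE documented with positive CTPA". A high-probability V/Q scan also qualifies, and death, return visits and hospitalization are sought as well.
- **Primary criterion** (same section, adjudication paragraph): "The primary criterion of a VTE event will be based on an objective diagnosis of DVT on Doppler ultrasonography, an intraluminal defect on CTPA". A high-probability V/Q scan also qualifies.
- **Deaths** (same paragraph): for deaths without evidence of VTE, the committee "will adjudicate whether or not the death is likely related to a PE". It adds: "A sudden death in the absence of other obvious cause will be adjudicated as related to a PE".
- **Analysis definition** (Statistical analysis): "VTE events will be defined by: DVT (assessed by proximal compression ultrasonography) or PE (a CTPA or angiography showing intraluminal defect". Again a high-probability V/Q scan also qualifies. Non-inferiority is then judged on the upper bound of the two-sided 90% interval for the between-group difference in the percentage of these events, against 1.5 points.

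**The concern.** The adjudication paragraph and the Statistical analysis section both claim to define the primary event, and they disagree. The first accepts DVT on Doppler ultrasonography without a level. The second accepts DVT on proximal compression ultrasonography only, and adds angiography for PE. A DVT below the proximal veins would count under one and not under the other. A DVT shown only on venous CT is sought at follow-up but appears in neither.

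The second gap is fatal PE. The committee classifies deaths as PE-related or not, but the headline outcome is a diagnosed VTE and every event list consists of imaging findings. The missing-as-event rule does not close the gap: it applies only to the secondary intention-to-treat analysis, and a known death is not a missing value. An analyst who follows the Statistical analysis section to the letter would count an adjudicated PE death without imaging as a non-event. Such a death would be the most serious failure of a rule-out strategy.

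If these choices stay open until the data are seen, the endpoint could be settled with the result in view.

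**Working it through.** **1. The lists side by side**

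| Item | Follow-up capture | Primary criterion (adjudication) | Analysis definition |
|---|---|---|---|
| DVT by ultrasound | lower limbs, no level | Doppler, no level | proximal compression only |
| DVT by venous CT | yes | not listed | not listed |
| PE by CTPA | yes | yes | yes |
| PE by angiography | not listed | not listed | yes |
| PE by high-probability V/Q | yes | yes | yes |
| PE-related death | death sought | adjudicated, but not in the event list | not listed |

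The conflict over what is analysed lies between the last two columns.

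**2. Inputs**

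- Control rate 1.5% and margin 1.5 points (end of Statistical analysis).
- One-sided alpha 5%, power 80%, 1624 before inflation, design effect D = 1.118, 5% non-evaluable, total 1920 (Sample size under non-inferiority hypothesis).

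**3. The plan's own figure reproduces**

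n per arm = (1.645 + 0.842)² × 2 × 0.015 × 0.985 / 0.015² = 812, so 1624 in total. Then 1624 × 1.118 / 0.95 = 1911, or 63.7 per cluster over 30 clusters. Rounded up to 64, this gives 64 × 30 = 1920. The endpoint problem does not touch this arithmetic.

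**4. Expected events**

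Evaluable per arm: 1920 × 0.95 / 2 = 912. Expected control events: 0.015 × 912 = 13.7, about 14.

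**5. Sensitivity to single events**

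Upper limit = (xI − xC)/912 + 1.645 × √{D × [pC(1 − pC) + pI(1 − pI)]/912}, where xC and xI are the control and intervention events and p = x/912. D = 1 is the unclustered Wald interval; D = 1.118 applies the protocol's design effect to the variance.

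| Control v intervention events | Upper limit, D = 1 | Upper limit, D = 1.118 |
|---|---|---|
| 14 v 14 | 0.95 | 1.00 |
| 14 v 17 | 1.32 | 1.38 |
| 14 v 18 | 1.45 | 1.51 |
| 14 v 19 | 1.57 | 1.63 |

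With 14 control events the conclusion changes between 18 and 19 intervention events unclustered, and between 17 and 18 with D = 1.118. These event counts are illustrative. They show how fragile the result is to any few events, not how many this ambiguity would move.

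**6. Power if a broader definition raises the rate**

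Effective n per arm at 1920: 912 / 1.118 = 815.7. Power = Φ(0.015 / √[2p(1 − p)/815.7] − 1.645), with the same assumed true rate p in both arms:

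- p = 1.5%: 80%
- p = 1.75%: 75%
- p = 2.0%: 70%

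**The case against.** The strongest defence concerns deaths. A reader might infer that the plan discards fatal PE. The documents do not support that as the intention. The adjudication paragraph introduces the committee's work as confirming the primary endpoint and then extends it to deaths without evidence of VTE. The secondary outcome is mortality at 3 months, which needs no cause of death, so the sudden-death rule has no evident use except for the primary endpoint. PE deaths were probably meant to count. What stands is that no definition says so, and the one tied to the decision rule lists imaging findings only.

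A reader might also infer three rival endpoint definitions. The follow-up list, however, describes what the interview and records review will look for. A wide capture net that feeds a narrower endpoint is not a contradiction. The same applies to distal DVT: no section names it, and its inclusion is inferred from ultrasound wording without a level.

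Third, a reader might infer that this ambiguity would by itself move the four or five events that tip the result. The documents give no count of non-proximal DVT or DVT on venous CT. On deaths, the Discussion points to few. It cites PE deaths in 0.2% of patients tested, which is 0.002 × 912 ≈ 1.8 per arm if that rate applied here. It puts the added risk in the experimental group below 1 in 10,000 at 30 days, which is under 0.1 death per 912.

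Finally, leaving out an event type does not always favour non-inferiority. If the type is equally frequent in both arms, the expected difference is unchanged and only the variance falls. A shift in the expected difference needs an excess of that type in the PERC arm, which is plausible for missed PE but not shown for non-proximal DVT.

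**Conclusion.** The inconsistency is real and is in the current text. The primary criterion and the analysis definition differ on DVT level and on angiography, neither places DVT found on venous CT, and the status of an adjudicated PE death is never stated. This is not detail left to an analysis plan, because the article itself fixes the event in conflicting ways.

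The size of the effect is unknown. What can be shown is that, with about 14 expected events per arm, an intervention excess of four or five events separates success from failure. This rests on the planned 1.5% control rate, 912 evaluable patients per arm and a Wald interval, either unclustered or with the protocol's design effect. Neither the claim that fatal PE was meant to be excluded nor the claim that the ambiguity would reverse the result follows from the documents. The point still merits correction, because the primary result could depend on a choice that the protocol leaves open.

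**What to change.** Before analysis, and without knowledge of results by group, adopt one committee-adjudicated primary endpoint and use it in both Trial objectives and outcomes and Statistical analysis.

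- Say explicitly that a death adjudicated as PE-related, including otherwise unexplained sudden death, is a primary event.
- State whether non-proximal DVT, DVT on venous CT and PE on angiography count.
- Choose the DVT scope that matches the definition behind the 1.5% control rate and the 1.5-point margin. The article does not give the definition used in the cited cohorts, so the sponsor must check it.
- Analyse the other DVT scope as a sensitivity analysis.
- Do not restrict the endpoint to symptomatic events unless the protocol intends it; that word is in none of the definitions.

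Deaths and VTE reports already go to the committee, which is blinded to study group, so the change needs a protocol clarification and no new data source. The cost is possible loss of power: a broader definition may raise the event rate, and at an assumed 1.75% in both arms power with 1920 patients would be about 75% rather than 80%.

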### Sample size under non-inferiority hypothesis

To assess non-inferiority of the “PERC strategy,” with 1-sided alpha = 5 %, beta = 20 %, *N1* = 1624 subjects are needed (East 6, Cytel, Cambridge, MA, USA). A cluster is a 6 months period for 1 site. Under the assumption of an intraclass correlation coefficient of 0.002, an intra-period correlation of 0.001 and a mean cluster size for one period of 60 patients, the cluster design effect would be of *D* = 1.118. Considering 5 % of non-evaluable subjects, with 15 sites involved in the trial, which corresponds to 30 clusters, 61 subjects per site per period are required and will lead to a total of 1920 patients.

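### The stated one-sided alpha of 5 % and power of 80 % are not both attained at N1 = 1624: a Wald bound keeps the power with about 5.6 % error, a score bound keeps the error with about 76–77 % power

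*Protocol article*

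**What the plan says.** In the Protocol article, Statistical analysis, the criterion is introduced with "The decision rule will be based on the upper bound of the" confidence interval; in full, this is the "upper bound of the 90 % 2-sided CI of the difference of percentage of VTE events between groups". Non-inferiority is rejected if that bound exceeds 1.5 points. The type of interval is not named. The section adds one test by name: "The Dunnett and Gent chi square test will also be performed". A GEE with clustering by site is to follow as a confirmatory analysis.

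The planning values stand at the end of the same section: "we estimate that the primary endpoint rate in our control group will be 1.5" %, and "the maximal difference in proportions between 2 groups (Delta) should not exceed 1.5" %, which puts the null point at 3.0 % against 1.5 %.

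Sample size under non-inferiority hypothesis sets "1-sided alpha = 5 %, beta = 20" % and concludes that "1624 subjects are needed". It then applies a cluster design effect of 1.118 and a 5 % allowance for non-evaluable patients, and gives a total of 1920.

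**The concern.** With so few expected events, a large-sample formula for a risk difference can promise properties that the analysis does not have. The Wald standard error is computed from the observed rates. When the PERC arm happens to have few events, the observed difference and its standard error are both small, so the upper bound falls below the margin more often than the nominal 5 %. That error is in the unsafe direction, because it declares non-inferiority when the true excess equals the margin. A bound that uses the variance under the null avoids this, but it has less power at the same size.

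If the quoted N1 rests on the first kind of variance, the quoted alpha and power may not both be true of the decision that the trial will make.

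**Working it through.** **Inputs.** Control rate 1.5 %, no true difference for power, and margin 1.5 points (Statistical analysis). One-sided alpha 5 %, power 80 %, N1 = 1624, design effect 1.118, 5 % non-evaluable and total 1920 (Sample size). Equal arms, since each site contributes one period of each strategy.

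**Step 1: reproduce N1.** The unpooled normal approximation gives

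n per arm = (1.645 + 0.842)² × 2 × 0.015 × 0.985 / 0.015² = 811.98, so 812 per arm and 1624 in total.

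This is an exact match. Expected events under equality are 812 × 0.015 = 12.2 per arm.

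**Step 2: the same calculation with null-restricted variance (Farrington-Manning).** The restricted rates are 2.56 % and 1.06 %:

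n per arm = [1.645 × √(0.0256 × 0.9744 + 0.0106 × 0.9894) + 0.842 × √(2 × 0.015 × 0.985)]² / 0.015² = 916.1 with unrounded inputs, so 917 per arm and 1834 in total.

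So 1624 corresponds to Wald-type variance and not to score-type variance.

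**Step 3: exact operating characteristics at 812 per arm.** For each rule, sum Bin(x; 812, p_PERC) × Bin(y; 812, p_control) over all pairs of counts (x, y) at which the rule declares non-inferiority. Power is taken at 1.5 % in both arms, and error at p_PERC = p_control + 1.5 points. Patients are independent.

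| Rule | Power, 1.5 % v 1.5 % | Error, 3.0 % v 1.5 % |
|---|---|---|
| Wald | 80.3 % | 5.64 % |
| Dunnett-Gent (z form) | 80.3 % | 5.64 % |
| Score (Farrington-Manning or Miettinen-Nurminen) | 76.5 % | 4.86 % |

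Wald and score bounds give different verdicts in 3.8 % of trials under equality.

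**Step 4: is this a quirk of one n?** Averaged over 800 to 830 per arm, Wald error is 5.6 % (range 5.5–5.8 %), score error is 4.9 % (4.7–5.0 %) and score power is 77.0 % (76.4–77.8 %). The score bound reaches 80 % exact power at about 880 per arm.

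**Step 5: does the inflation help?** The total of 1920 gives 960 × 0.95 = 912 evaluable per arm, and 912 / 1.118 ≈ 816 effective. At 816 the score bound has 76.5 % power and Wald error is 5.5 %. Score power passes 80 % (80.8 % at 912) only if clustering is ignored.

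**Step 6: lower control rates.** These rates are assumptions; the article plans only for 1.5 %. Wald error with a true excess of 1.5 points:

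| Control rate | Wald error |
|---|---|
| 1.0 % | 6.0 % |
| 0.5 % | 7.0 % |
| 0.2 % | 7.8 % |
| 0.1 % | 8.2 % |

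The score bound stays below 5 % at all of these rates. Its power under equal rates is 87.6 % at 1.0 % and 97.9 % at 0.5 %.

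**The case against.** The best reply is that the article never says the interval is Wald. It fixes the confidence level, the estimand and the threshold, and the choice of interval commonly belongs to the analysis plan. Sizing with a normal approximation is standard and does not bind the analysis. All of this stands: the missing name is no fault in itself, and "1624 subjects are needed" follows correctly from a standard formula. What remains is that the choice left to the analysis plan decides which stated property fails at the planned rate. Among the rules examined, none rescues both.

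Three stronger readings are tempting, and the article does not support them:

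- *The trial's false non-inferiority rate is 7–8 %.* This needs both a Wald bound and a control rate of about 0.5 % or lower, a third or less of the planned 1.5 %. At such rates a score bound meets both targets comfortably, so the conflict between alpha and power is confined to the neighbourhood of the planned rate.
- *The trial needs 1834 patients before inflation.* The restricted-variance formula overstates the exact requirement, which is about 880 per arm, or 1760.
- *The stated pair holds as long as a Wald interval is used.* Wald keeps the power but not the 5 % error, and Dunnett-Gent does the same at the planned rate.

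It is also fair to say that the enumeration assumes independent patients. It describes N1, which is itself the figure before clustering, and not the full clustered analysis.

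**Conclusion.** The point holds, with minor to moderate severity. At N1 and the planned rates the stated alpha and power do not hold together. The discrepancy is about 0.6 points of error (5.64 % against 5 %) with a Wald bound or the Dunnett-Gent test, or about 3.5 points of power (76.5 % against 80 %) with a score bound. The named Dunnett-Gent test is therefore no safeguard for a Wald bound at the planned rates, because it has the same error there.

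The result rests on equal arms of 812, independent patients, and a true rate of 1.5 % in both arms for power. It also assumes that the inflation to 1920 is fully used by clustering and non-evaluable patients.

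**What to change.** In Statistical analysis, name the deciding bound as the upper limit of the two-sided 90 % score-type interval for the risk difference (Miettinen-Nurminen or Farrington-Manning), with clustering handled as the plan already intends. In Sample size under non-inferiority hypothesis, state that N1 = 1624 gives about 76–77 % power with that bound at the planned 1.5 % rate.

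Dropping the Dunnett-Gent test, or passing effective sample sizes to the interval, is a matter of preference and is not needed for this point.

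The cost is a change of wording, a different interval routine and a slightly less favourable stated power. No patients are added. Restoring 80 % with the score bound would take about 1760 before inflation, that is 1760 × 1.118 / 0.95 ≈ 2071 in total against the stated 1920; the wording change does not require this.

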### Experimental plan

Each center will be randomized for the period: a 6-month intervention period followed by a 6-month control period, or a 6-month control period followed by a 6-month intervention period. The randomization will be prepared by URC-Est using permutation blocks (SAS 9.3, SAS Inc., Cary, NC, USA) before the first site initiation visit. The design, conduct and reporting of this study will follow the Consolidated Standards of Reporting Trials (CONSORT) statement extended to cluster randomized trials [32]. The two groups will have a different work-up for the diagnosis of PE in the ED as follows:Control group: standard strategy: conventional PE work-up. Every low-risk patient will undergo sensitive D-dimer testing, with subsequent CTPA if positive. In case of negative D-dimer, PE will be considered as excluded (Fig. 2a).Intervention group (PERC-based strategy): PE work-up based on the use of the PERC rule. If all PERC criteria are negative, no further testing for PE will be recommended. If at least one criterion is positive, then the patient will undergo sensitive D-dimer testing, with subsequent CTPA if positive. In case of negative D-dimer result, PE will be considered as excluded (Fig. 2b).

It has been recently reported that the cut-off for positive D-dimer should be changed for patients aged > 50 years to age × 10 ng/ml [33]. This strategy has been validated in a large multicenter international trial [34]. This strategy is actually endorsed by our centers. The strategy for defining “positive D-dimer” (age × 10 ng/ml for patients older than 50 years) will be stated before the start of the study in each center and not changed during the whole study period. Of note, this change will only concern patients aged 50 years or greater, i.e. with a PERC > 0. As this will not affect PERC-negative patients, there will be no interference with our objectives.

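### No cluster adjustment is stated for the 90% confidence interval that decides non-inferiority, and the protocol does not say whether that interval or the cluster-adjusted GEE governs

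*Protocol article*

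**What the plan says.** All references are to the protocol article.

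- **Design (Experimental plan).** The site is the unit of allocation: "Each center will be randomized for the period: a 6-month intervention period followed by a 6-month control period", or the reverse order.
- **Decision rule (Statistical analysis).** The decision rests on the upper bound of the 90% "2-sided CI of the difference of percentage of VTE events between groups". Non-inferiority is rejected if that bound exceeds 1.5 percentage points. The section then adds: "The Dunnett and Gent chi square test will also be performed". No site or period term is given for either.
- **Clustering for the primary endpoint (same section).** After a sentence on the intention-to-treat analysis comes: "Considering cluster randomization, confirmatory analysis will be performed using a generalized estimating equation (GEE) assuming an exchangeable correlation matrix structure", with clustering at site level. Nothing says which result governs if the GEE and the interval differ.
- **Sample size under non-inferiority hypothesis.** "A cluster is a 6 months period for 1 site". The section assumes an intraclass correlation of 0.002, an intra-period correlation of 0.001 and 60 patients per site-period. It derives a design effect of 1.118, "with 1-sided alpha = 5 %, beta = 20" %.
- **Secondary outcomes.** For length of stay, admissions, imaging, adverse events and deaths, the mixed model or GEE is itself the comparison.

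**The concern.** Patients in the same site and period are assumed to be correlated, and the sample size pays for that correlation. An interval for the difference of two percentages that treats patients as independent leaves out the same variance. A chi-square test for independent observations does so too. If that interval decides the trial, its upper bound sits slightly too low. The error then runs towards declaring non-inferiority wrongly, in a safety comparison that already uses a one-sided 5% level.

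The second problem is precedence. Two analyses of the same endpoint are planned, one with and one without a stated allowance for clustering. A result near the 1.5-point margin could pass one and fail the other, and the choice between them would be made with the data in view.

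**Working it through.** **1. Reproduce the plan's figures.** Inputs: 1.5% in both groups, margin 1.5 points, one-sided 5%, power 80%.

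- Per arm: n = 2 × 0.015 × 0.985 × (1.645 + 0.842)² / 0.015² = 812, so 1624 in total, as stated.
- Design effect: D = 1 + (60 − 1) × 0.002 = 1.118, as stated. The 0.001 is not used.
- 1624 × 1.118 = 1815.6. Divided by 30 site-periods this is 60.5, rounded up to 61. For the total, 1815.6 / 0.95 = 1911.2; divided by 30 this is 63.7, rounded up to 64; and 64 × 30 = 1920, as stated.

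**2. Design effect for a crossover of sites.** With m patients per site-period, D = 1 + (m − 1) × ICC − m × (between-period correlation). Reading 0.001 as the within-site, between-period correlation (my reading; the article calls it intra-period) gives D = 1 + 59 × 0.002 − 60 × 0.001 = 1.058. The protocol's own values therefore support 1.058 to 1.118.

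**3. Effect on an unadjusted interval.** The correct standard error is √D times the unadjusted one. The actual one-sided error is 1 − Φ(1.645/√D). Half-widths use 15 × 61 = 915 evaluable patients per arm and 1.5% in both groups.

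| D | Width factor √D | 90% half-width (points) | One-sided error | Coverage |
|---|---|---|---|---|
| 1 (unadjusted) | 1.000 | 0.935 | 5.0% | 90.0% |
| 1.058 | 1.029 | 0.961 | 5.5% | 89.0% |
| 1.118 | 1.057 | 0.988 | 6.0% | 88.0% |

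The upper bound moves by about 0.03 to 0.05 points, so the decision changes only for a result that close to the margin.

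**4. Simulation at the margin.** 15 sites, two periods, 61 patients each, 1.5% v 3.0%, gamma-distributed site and site-period effects, 200,000 runs. Entries are the percentage of runs that wrongly declare non-inferiority.

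| ICC / between-period correlation | Raw 90% CI | Site-level paired difference, uncorrected SE, normal quantile | Site-level paired difference, corrected SE, t on 14 df |
|---|---|---|---|
| 0 / 0 | 5.5 | 7.4 | 5.5 |
| 0.002 / 0.001 (protocol) | 6.3 | 7.7 | 5.7 |
| 0.002 / 0 | 6.7 | 7.7 | 5.8 |
| 0.005 / 0.0025 (assumed) | 7.4 | 8.3 | 6.3 |
| 0.01 / 0.005 (assumed) | 9.7 | 9.5 | 7.3 |

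- The raw interval already errs at 5.5% with no clustering. That half point comes from the normal approximation with rare events. At 0.002/0.001, clustering adds about 0.7 points.
- The uncorrected site-level column stands in for a robust GEE variance without a small-sample correction. With 15 sites it does worse than the raw interval at the protocol's values, so adjustment helps only if it is corrected.

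**5. Where the direction reverses.** If the between-period correlation equals the ICC, D = 1 + 59 × 0.002 − 60 × 0.002 = 0.998, and by this formula the raw interval is not too narrow.

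**6. Power.**

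- Analytic, with 1920 × 0.95 / 2 = 912 per arm and a normal quantile: 82.0% at D = 1.058 and 80.2% at D = 1.118.
- Simulated at 1.5% in both groups, 0.002/0.001: 83% for the raw interval and 79% for the paired difference with t on 14 df.
- Simulated at 0.002/0, which corresponds to the stated D = 1.118: 82% and 77%.

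**The case against.** **The text never says that the deciding interval is unadjusted.** This stands. That reading is an inference from three facts: no cluster term is given, the accompanying test is for independent observations, and the GEE is introduced separately. A reader might infer that the protocol prescribes a naive interval. It does not say so, and the word confirmatory could even mean that the GEE is the inferential analysis. On either reading the protocol fails to say which analysis decides.

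**Link function, period term and small-sample correction belong in an analysis plan.** This stands. Their absence from an article is not an error. In particular, nothing supports assuming a logit link, and hence a result on the odds-ratio scale. They matter here only as parts of a workable fix.

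**Clustering is partly handled.** This also stands. The sample size is inflated, and the GEE clusters by site, which keeps both periods of a site together. What is missing is the link from that analysis to the decision rule.

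**The effect is small and conditional.** This is correct. A reader might infer error rates of 7–10% for the raw interval. Those need ICCs 2.5 to 5 times the protocol's 0.002, and no document supports them. Part of the simulated excess is not due to clustering at all.

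**The gain from the fix is small and costs power.** At the protocol's correlations the corrected analysis lowers simulated error only from about 6.3% to 5.7%, and power drops just below target. The gain is real but modest. The stronger reason to act is to settle in advance which interval decides.

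**Conclusion.** The concern holds in a limited form: it should be fixed, but it does not undermine the design. The decision rule as written carries no stated allowance for the variance that the sample size assumes, and no rule gives either the interval or the GEE precedence.

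If the interval is computed without adjustment, it is about 3–6% too narrow and the analytic one-sided error is 5.5–6.0%. In simulation the error is about 6.3%, of which about half a point is the rare-event approximation. This rests on the protocol's ICC of 0.002, on a between-period correlation of 0.001 or 0, and on about 60 patients per site-period. It would be larger with higher ICCs, for which the document gives no basis, and by the design-effect formula absent if the two correlations are equal. It is therefore not established that the nominal 5% must be exceeded, only that it is exceeded under the protocol's own assumptions.

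**What to change.** State in the decision rule that the 90% interval compared with the 1.5-point margin is a cluster-adjusted risk difference that keeps both periods of a site together and carries a small-sample correction for 15 sites. Two suitable forms are:

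- an identity-link GEE with a period effect, a bias-corrected sandwich standard error and t quantiles;
- a within-site paired difference with t quantiles, which also serves as a fallback if the GEE does not converge with so few events.

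Say explicitly that this interval governs, and label the raw interval and the Dunnett and Gent test as supportive.

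The cost is a change of wording and a slightly wider interval. Simulated power falls from about 83% to about 79% at the protocol's correlations (about 77% if the between-period correlation is zero), against the planned 80%. The planned 1920 patients come close to covering the adjustment, and the small shortfall should be stated.
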